## Abstract

**Background:**

Although the prevalence of psychological problems in transitional-age youth (i.e., youth aged 15 to 25; TAY) is high, TAY are much less likely to receive age-appropriate treatments for their psychological problems compared to younger adolescents or older adults. Hence, effective interventions for TAY seem warranted. ACT your way is a transdiagnostic treatment, specifically developed for TAY, based on the principles of Acceptance and Commitment Therapy (ACT). ACT your way is not directed primarily at symptom reduction, but mainly aims to change the underlying mechanism of psychopathology, namely increasing TAY’s psychological flexibility. Meta-analyses show that ACT is an effective treatment for adults with diverse types of psychopathology. Less is known about the effectiveness of ACT for TAY. Therefore, the goal of this study is to examine the effectiveness and cost-effectiveness of ACT your way. In addition, we will investigate for whom and under what circumstances (i.e., moderators) and how (i.e., mediators) the intervention is (most) effective.

**Method:**

The study is designed as a multi-centre, randomized controlled trial. In total, 140 TAY diagnosed with any psychological disorder will be randomly assigned to either the ACT your way or treatment as usual (TAU) condition. In total, six assessments will be conducted: at baseline, after 3, 6 and 9 sessions, at post-intervention and at 6-month follow-up, using multiple informants (TAY, parents/caregivers, therapists). Assessments will include diagnostic interviews and questionnaires. The primary outcomes are psychological flexibility and number of DSM-5 diagnoses; the secondary outcomes are the presence of the primary DSM-5 diagnosis, psychopathology, personality problems, global, individual and societal functioning, quality of life, stress, treatment satisfaction, treatment drop-out and therapeutic alliance. We will also assess costs and various moderators (i.e., demographic characteristics, type and severity of problems, psychopathology of parents/caregivers, treatment expectancy and previous treatments) and mediators (i.e., psychological flexibility, emotion regulation, self-compassion, autonomy, perfectionism, self-esteem and group cohesion).

**Discussion:**

To our knowledge, this is the first study investigating the (cost-)effectiveness of ACT compared to TAU in clinically referred TAY with various types of psychopathology, using a rigorous design.

**Trial registration:**

The research project is registered in the Dutch Trial Register (Trial NL9642).

The developmental period of middle adolescence to early adulthood is a crucial period characterized by significant variability and change. During this period, youths make many important life choices and develop various habits that could affect their later (mental) health [1]. Moreover, in this life stage, youths face numerous developmental and psychosocial challenges, such as finishing their education, choosing a career, building new (romantic) relationships and becoming self-reliant. Also, psychological restructuring takes place that is often associated with identity crisis, risk behaviour and emotional instability [2]. Due to these significant and often stressful changes, transitional-age youth (i.e., youth aged 15 to 25; TAY) are at great risk of developing new psychological problems or persisting to experience psychological problems they developed during childhood [2, 3]. To illustrate, in 2021, eighteen percent of the Dutch adolescents and young adults indicated to be mentally unhealthy (e.g., stressed, anxious or depressed) [4]. Moreover, results from the global burden of disease study show that the burden of psychological disorders peaks between middle adolescence and young adulthood [5]. These elevated prevalence rates of psychological disorders in TAY are problematic, as many psychological disorders persist into adulthood, cause comorbid disorders [6–8] and are strongly related to other health and developmental concerns in youths (e.g., lower educational and work achievements, troubles with law, social isolation, suicide, substance abuse and violence) [6, 9]. Hence, the transitional-age period is a particularly important period for intervening effectively.

Although the prevalence of psychological problems in TAY is high, TAY are much less likely to receive treatment for their psychological problems compared to younger adolescents or older adults [10, 11]. Moreover, when TAY receive treatment for their psychological problems, they are significantly more likely to drop-out compared to older adults [12]. Also, in many countries, the collaboration between youth (i.e., below the age of 18) and adult (i.e., 18 years or older) mental health care facilities is not optimal, resulting in no or poor transitions from youth- to adult care after adolescents turn 18. These poorly executed transitions threaten the continuity of psychological care for TAY in this already challenging and critical developmental period [13, 14]. Additionally, when TAY are referred for treatment, they often receive evidence-based interventions developed for either youth (i.e., below the age of 18) or adults (i.e., 18 years or older) [15, 16]. These evidence-based interventions do not meet TAY’s needs and are often not developmentally sensitive. Therefore, effective interventions specifically developed for TAY seem warranted.

There are several important aspects that could be considered when developing a suitable treatment for TAY. First, in a qualitative study, TAY indicated that an important barrier for active participation in mental health care was having a therapist who acts as an authority figure, has little interest in the TAY’s perspective and does not stimulate the TAY to participate in the decision making [17]. Hence, when developing interventions for TAY, it is important to consider the TAY’s perspective and stimulate TAY to participate in framing the therapy. Second, during the transitional-age period, TAY need to form an identity and become self-reliant autonomous figures [2]. Therefore, a strong focus on identity and autonomy development within interventions for TAY seem warranted. Third, as the transitional-age period is a period of significant variability and change, TAY’s psychological problems are often complex and changeable. For instance, during the course of treatment new stressors, associated with various developmental challenges (e.g., finishing education, moving out of their parental home or ending a romantic relationship), often arise. These stressors could potentially cause the development of new or comorbid problems and alter TAY’s therapy needs [18]. Most current evidence-based interventions only focus on treating symptoms of one specific disorder, making these interventions less suitable for TAY with changing symptom profiles and comorbid problems. For these TAY, interventions targeting transdiagnostic mechanisms that underly the symptoms of multiple disorders might be more suitable. Such transdiagnostic interventions have a better fit with the complex and changeable psychological problems most TAY experience. Moreover, transdiagnostic interventions have potential benefits over traditional interventions as various psychological symptoms can be treated within one intervention, possibly contributing to the efficiency and (cost-)effectiveness of care [19]. Fourth, most current evidence-based interventions focus on the reduction of symptoms, making these interventions less suitable for TAY with recurrent of chronic psychological problems. For these TAY, interventions that focus on increasing quality of life or learning skills that help to build resilience might be more applicable.

ACT your way is a transdiagnostic intervention specially developed for TAY. Within ACT your way, therapists and TAY contribute equally to framing therapy goals and actions, possibly stimulating TAY to actively participate within the intervention. Furthermore, due to its strong focus on identity and autonomy development, the intervention fits well with the developmental needs of this age group. Moreover, the intervention is not aimed primarily at symptom reduction, but mainly at increasing quality of life and changing the underlying mechanisms of psychopathology. This makes the intervention also suitable for TAY with changing symptom profiles, comorbidity, and chronic or recurrent psychological problems.

ACT your way is based on the principles of Acceptance and Commitment Therapy (ACT). The main purpose of ACT is to increase psychological flexibility, a transdiagnostic mechanism which can be defined as an individual’s acceptance of negative feelings, thoughts and physical sensations, and the ability to choose an adaptive (and more effective) response [20]. More specifically, psychological flexibility contains six core processes: acceptance (i.e., learning to accept unpleasant emotions, thoughts and situations, instead of avoiding or fighting against them), defusion (i.e., changing the unwanted functions of thoughts, instead of changing their form, frequency or sensitivity), contact with the present moment (i.e., learning to focus on the here-and-now, instead of ruminating about the past or worrying about the future), self as context (i.e. developing a flexible view of the self, where content about the self can be observed and accepted), values (i.e., determining what is most important for oneself), and committed action (i.e., changing behaviour in the direction of ones values) [20]. In ACT, these six core processes are stimulated using psychoeducation, mindfulness exercises, metaphors and experiential exercises [20].

There are several meta-analyses showing that ACT is equally effective compared to well established evidence-based treatments (e.g., cognitive behavioral therapy; CBT) and superior to inactive control conditions (e.g., placebo or waitlist) and treatment as usual (TAU) in adults with depression, anxiety, pain, substance use and other types of psychopathology [21–24]. Moreover, in the United States, ACT is registered as evidence-based treatment for adults with chronic pain and depression [25]. Until now, less is known about the effectiveness of ACT for adolescents and young adults [26, 27]. Few studies investigated the effectiveness of ACT in adolescents and/or young adults with different types of problems, such as anorexia nervosa [28, 29], obsessive–compulsive anxiety [30], pain [31, 32], depressive symptoms [33, 34], autism spectrum disorder [35], social and school adaptation [36], social anxiety [37], posttraumatic stress [38], learning disabilities and anxiety [39], academic procrastination [40], trichotillomania [41], aggression [42] and antisocial behaviour [43]. These studies show promising effects. In addition, the effectiveness of the ACT your way intervention has recently been examined in a pilot study with 23 TAY with recurrent or chronic depression, who previously received CBT [44]. At posttreatment, 76.2% of the TAY did not meet the criteria for a depressive disorder anymore. Moreover, participants reported significant improvements in depressive symptoms, quality of life, perceived competence, and comorbid internalizing problems. In addition, the treatment drop-out was remarkably less (20.6%) compared to treatment drop-out in a CBT trial for the same target group of 12 to 21 year olds (ranging from 41 to 57%) [45]. Hence, results in terms of the effectiveness of ACT your way specifically, also seem promising. However, many of the abovementioned studies lack an adequate sample size, do not use a control group or randomisation, or are case studies. Furthermore, no research has been done in TAY with a wide range of psychological disorders, including comorbid, chronic and/or recurrent diagnoses. In addition, the cost-effectiveness of ACT in TAY has never been studied before.

Therefore, the first aim of this study is to evaluate the effectiveness of ACT your way in TAY with a wide range of psychological disorders. In this study, ACT your way will be compared to TAU. We expect that, compared to TAU, ACT your way shows more improvements in our primary (i.e., psychological flexibility and the number of DSM-5 diagnoses) and secondary outcomes (i.e., the presence of the primary DSM-5 diagnosis, psychopathology, personality problems, global functioning, individual and societal functioning, quality of life, stress) at the short term (immediately after the intervention), but also at the long term (after six months). Furthermore, we expect more treatment satisfaction, less treatment drop-out and better treatment alliance (i.e., also secondary outcomes) of TAY since ACT your way is more attuned to their needs. The second aim is to examine the cost-effectiveness of ACT your way. We expect that ACT your way is more cost-effective than TAU, because, compared to carrying out multiple diagnosis-specific interventions, ACT your way can treat various problems at once [18].

The third aim is to investigate for whom and under what circumstances ACT you way works best by testing possible moderators (i.e., demographic characteristics [age, gender, education level and ethnicity of TAY], type and severity of problems, psychopathology of parents/caregivers, treatment expectancy and previous treatments). Moderators are baseline characteristics that interact with the type of treatment (i.e., ACT your way or TAU) to affect outcome. As most prior studies investigating the effects of ACT do not compare ACT to active treatments, the knowledge on treatment moderators is scarce. Based on existing findings, we expect that TAY with severer problems (i.e., higher baseline levels of psychopathology and/or more comorbid problems) will benefit more from ACT your way than from TAU [46–49]. Due to contrasting (e.g., [47, 50]) or insufficient findings in earlier research, no hypotheses are formulated regarding the moderating roles of demographic characteristics (age, gender, education level and ethnicity of TAY), type of problems, psychopathology of parents/caregivers, treatment expectancy and the number of previous treatments.

The fourth aim is to examine through which mechanisms ACT your way works by testing possible mediators (i.e., psychological flexibility, emotion regulation, self-compassion, autonomy, perfectionism, self-esteem and group-cohesion). Based on studies investigating mediators of the effectiveness of ACT, we hypothesize that ACT your way will increase TAY’s psychological flexibility [51, 52], emotion regulation [53, 54] and self-compassion [55, 56] which, in turn, will affect the primary (e.g., number of DSM-diagnoses) and secondary outcomes (e.g., quality of life). To our knowledge, there are no studies investigating if the effects of ACT are mediated by the clients’ autonomy, perfectionism, self-esteem and group cohesion. Notwithstanding, there are studies showing that ACT can decrease the clients’ perfectionism [57, 58] and increase the clients' self-esteem [40, 44, 59, 60], and that individuals with higher levels of perfectionism and lower levels self-esteem more often experience psychological problems than individuals with lower levels of perfectionism and higher levels of self-esteem [61, 62]. Hence, we also expect that ACT your way will decrease TAY’s perfectionism and will increase TAY’s self-esteem, which, in turn, will improve the primary (e.g., number of DSM-diagnoses) and secondary outcomes (e.g., quality of life). Due to insufficient findings in earlier research, no hypotheses are formulated regarding the mediating roles of autonomy and group cohesion.

## Method

The study will be reported in accordance with the CONSORT 2010 statement [63]. The research project is approved by the Medical Research Ethics Committee NedMec (NL78679.041.21) and registered in the Dutch Trial Register (Trial NL9642).

### Participants

In total, 140 TAY with any psychological disorder (e.g., anxiety disorder, obsessive–compulsive disorder (OCD), trauma, depressive disorder, persistent depressive disorder, oppositional defiant disorder (ODD), conduct disorder (CD), personality disorder, autism spectrum disorder or any combination of these) will be included in the study. Also their parents/caregivers and therapists will be asked to participate. Participants will be recruited between March 2022 and March 2024.

#### Inclusion and exclusion criteria

Inclusion criteria for the TAY are (1) having a psychological disorder, (2) being 15 to 25 years old, (3) being referred to one of the participating mental healthcare institutions. Exclusion criteria are (1) having insufficient knowledge of the Dutch language, (2) acute suicide risk, (3) currently meeting the criteria for a DSM-5 substance abuse, psychotic and/or bipolar disorder, (4) having an estimated IQ below 80, (5) unstable medication (i.e., the medication should be set before the start of the intervention and should remain stable during the intervention), (6) absence of TAY’s or parental permission (for adolescents below the age of 16).

#### Sample size calculation

We calculated the sample size for a two-level multilevel analysis, using the Optimal Design program [64]. In accordance with our planned analyses, the first level represents the TAY and the second level represents the therapists. As most of the therapists either give the ACT your way or the TAU intervention, we calculated the sample size as for a cluster RCT in which the therapists represent the clusters. Within our sample size calculation, we used a cluster size (i.e., the expected number of therapists) of 70, as we expect that in both conditions approximately 35 therapists will be carrying out either the ACT your way or TAU intervention. In addition, we used an ICC of 0.05 as this is the average ICC reported in meta-analyses of therapist effects in psychological intervention research [65]. Furthermore, the effect size is based on a meta-analysis in which 39 RCT’s were included that investigated the efficacy of ACT, including 1,821 adults with various mental disorders [21]. We based the effect-size on this meta-analysis as, to our knowledge, this is the most recent meta-analysis examining the effects of ACT transdiagnostically. When ACT was compared to TAU a medium effect was found (Hedges g = 0.64), when ACT was compared to CBT a small effect was found (Hedges g = 0.32). In this study ACT will be compared to TAU, presuming a medium effect around 0.64. However, since we want to be conservative and expect that, at least with some of the participants, CBT will be used in TAU as well, an effect size of 0.50 was included in the sample size calculation. Hence, with a cluster size of 70, an effect size of 0.50, an ICC of 0.05, an α of 0.05 and a power of 0.8, a sample size of 140 (i.e., on average two TAY per therapist, and 70 TAY per condition) is assumed.

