#### Effectiveness

The effect of the intervention on the primary (i.e., psychological flexibility and number of DSM-5 diagnoses) and secondary outcomes (i.e., presence of the primary DSM-5 diagnosis, psychopathology, personality problems, global functioning, individual and societal functioning, quality of life, stress, treatment satisfaction, drop-out and therapeutic alliance) will be evaluated using a two-level multilevel analysis in Mplus [115]. Specifically, we will investigate, if condition (i.e., ACT or TAU) predicts the post-intervention (T4) and 6-month follow-up (T5) levels of our primary and secondary outcomes, while controlling for the baseline levels of the concerning outcomes. We will perform a two-level multilevel analysis as we expect that TAY will be nested within therapists. Hence, the first level will represent the TAY and the second level will represent the therapists. We do not expect variance at the measurement level, as the analyses will be performed separately for the post-intervention and 6-month follow-up assessments. Although we expect that therapists will be nested within institutions, we will not include a third level as the number of institutions in our study is too small (i.e., 14 institutions). Instead, in all analyses, we will add dummies representing the mental healthcare institutions.

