The presented study design has some potential challenges that could turn into limitations if not handled properly. Hence, for each potential challenge, a solution to overcome this challenge will be discussed. First, in the current study, ACT your way will be carried out both in an individual as in a group format, making it more difficult to isolate intervention effects from treatment modality effects. We decided to carry out ACT your way both individually as in groups, as both treatment modalities have their own potential advantages. For instance, group interventions might provide more opportunities for normalization, positive peer modeling and social support, whereas within individual interventions, therapists can more easily adapt exercises and subjects to the specific wishes and needs of each client. To isolate intervention from treatment modality effects, we will perform additional analyses in which we explore possible differences between both treatment modalities (see Method section). Second, the TAU condition might be heterogeneous in content and duration, which makes it challenging to compare the effects of ACT your way with the effects of TAU. To address this challenge, we will ask all therapists in the TAU condition to write down the content and duration of each session. Subsequently, we will investigate if there are differences in duration between ACT your way and TAU. If there are differences, the duration of treatment will be added as covariate in all analyses. Third, recruiting a sample of 140 TAY in 24 months could be challenging. To reach this sample size, we will cooperate with fourteen mental health care institutions in the Netherlands and Belgium. Moreover, to promote participation, we will give TAY a 30 euro giftcard as a reward and only use online questionnaires that TAY, parents/caregivers and therapists can easily fill out at home. Last, non-response and/or drop-out can also be a potential challenge. To minimize non-response, we built a website, including a system that automatically sends research assistants weekly updates via mail, that helps research assistants to monitor the assessment progress. At the website and in the weekly updates, research assistants can easily see which questionnaires are filled out or not and which ones are planned. With the help of this website and automatic mailing system, researchers can directly react to non-response and increase the response rate of the study. To minimize measurement drop-out, we will motivate TAY to continue participating by sending them thank you emails and newsletters and handing out a 5 euro gift card after each assessment. Moreover, when participants drop out of treatment, we will still ask them to fill out the post-intervention and follow-up assessments. Furthermore, to avoid potential bias due to drop-out, all analyses will be carried out according to the intention to treat principle.

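### The sample size is set for one test at alpha 0.05, but the plan has four unranked primary tests and no primary time point or rule for combining them

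*Protocol article*

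**What the plan says.** **Sample size.** The Sample size calculation section treats therapists as clusters: "we used a cluster size (i.e., the expected number of therapists) of 70", 35 per condition, with two young people per therapist on average. It continues: "we used an ICC of 0.05 as this is the average ICC reported in meta-analyses of therapist effects", and "an effect size of 0.50 was included in the sample size calculation". It closes with "an α of 0.05 and a power of 0.8, a sample size of 140". One alpha is given. No loss of data and no baseline covariate enter the calculation.

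**Primary outcomes.** The Abstract states: "The primary outcomes are psychological flexibility and number of DSM-5 diagnoses". The aims at the end of the introduction name the same two outcomes, without ranking them, and expect superiority both directly after treatment and six months later.

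**Analysis.** Under Data analysis, Effectiveness, the model asks whether condition "predicts the post-intervention (T4) and 6-month follow-up (T5) levels of our primary and secondary outcomes", controlling for the baseline level of the outcome. T4 and T5 are analysed separately. The article states no primary time point, no order of testing and no rule for combining results.

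**Drop-out.** The Discussion says that "non-response and/or drop-out can also be a potential challenge" and gives no rate. It describes response monitoring and a gift card after each assessment, and says that those who stop treatment will still be asked for T4 and T5 data.

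**The concern.** Two outcomes at two time points make four primary tests of equal standing, while the sample size paragraph describes one. As written, nothing prevents a success claim on whichever of the four reaches significance, and the 5% level then no longer describes the risk of a false claim for the trial.

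If a correction is added later, the alpha per test falls, and the stated power of 0.8 no longer belongs to the analysis that is run. Either way, the sample size paragraph does not describe the primary analysis.

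**Working it through.** **Inputs, all from the Sample size calculation section:** d = 0.50 (SD 1), ICC = 0.05, J = 70 therapists, m = 2 young people per therapist, alpha = 0.05. Sidedness is not stated. Two-sided is assumed, because a one-sided test needs only about 100.

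**1. The plan's own figure.** For a two-level cluster design, λ = J·d² / [4·(ICC + (1 − ICC)/m)], and power comes from the non-central F(1, J − 2) distribution.
- J = 70, m = 2: λ = 70 × 0.25 / [4 × (0.05 + 0.475)] = 17.5 / 2.1 = 8.33; power 0.812.
- J = 68 (136 participants): power 0.801. J = 66 (132 participants): power 0.788.

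So 140 is correct for one test with everyone analysed.

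**2. Family-wise error over the planned tests.** Each test is taken at 5%, the only alpha stated, with any one significant result counting as success.
- Four independent tests: 1 − 0.95⁴ = 0.185.
- Four correlated tests (simulated multivariate normal statistics): as the correlation between time points goes from 0 to 0.7 and that between outcomes from 0 to 0.5 (both assumed), the error runs from 18.5% down to 14.9%. At 0.7 for both it is still 13.7%.
- Two outcomes at one time point: 1 − 0.95² = 0.0975 if independent, about 9% at a correlation of 0.5.

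**3. Power under a corrected alpha, with the planned baseline adjustment.** Adjustment for a baseline correlated r with the outcome is represented by dividing λ by (1 − r²). Loss of outcome data is represented by a smaller m (20% loss gives m = 1.6). The article gives neither r nor a loss rate, so both are assumptions. With two outcomes, the first Holm step is 0.05/2 = 0.025.

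| Alpha | Loss | Unadjusted | r = 0.3 | r = 0.4 | r = 0.5 |
|---|---|---|---|---|---|
| 0.05 | none | 0.81 | 0.85 | 0.87 | 0.91 |
| 0.05 | 20% | 0.73 | 0.77 | 0.80 | 0.84 |
| 0.025 | none | 0.72 | 0.77 | 0.80 | 0.85 |
| 0.025 | 20% | 0.62 | 0.67 | 0.71 | 0.76 |

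Example, 20% loss at alpha 0.05, unadjusted: λ = 17.5 / [4 × (0.05 + 0.95/1.6)] = 17.5 / 2.575 = 6.80; power 0.729. With r = 0.4: λ = 6.80 / 0.84 = 8.09; power 0.801.

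**The case against.** **Multiplicity may be handled elsewhere.** The article condenses a longer protocol, and an analysis plan that is not shown could hold a correction. The effectiveness section states no significance level, so testing each outcome at 5% is inferred from the sample size paragraph. This stands as a limit on the claim: the 15% to 18.5% is conditional. It does not remove the point. The sample size is fixed here on an uncorrected 0.05 for one test, so a correction made elsewhere would still leave the stated power describing a different analysis.

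**Power may not be short at all.** A reader might infer that drop-out and multiple testing together mean that the stated 0.8 is not reached. The documents do not support that.
- Testing four times at 5% does not lower the power of any one test. The alpha 0.025 figures arise only under the correction proposed here.
- The planned baseline adjustment was not counted in the sample size. It brings power back to 0.80 at alpha 0.05 and 20% loss if r is 0.4.
- The Discussion calls drop-out only a potential challenge. The 20.6% cited in the introduction for the pilot is drop-out from treatment, and such participants are still asked for outcome data. It does not fix a rate of missing outcomes.
- The effect size was lowered from about 0.64 to 0.50 to be conservative. At 0.64, power would be 0.85 even at alpha 0.025 with 20% loss and no adjustment.

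**T5 matters to the investigators.** The aims include the long term, so making T5 secondary is one choice among several. That is fair; what matters is that a choice is fixed in advance.

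**Wording of the cluster input.** Seventy is the number of clusters, not their size. The article explains this where it uses the term, so it is a labelling slip and does not affect the result.

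**Conclusion.** The concern holds as a mismatch between sample size and primary analysis, with uncontrolled error across the primary tests. The total of 140 is arithmetically right for one two-sided 5% test with complete data. The primary analysis contains four such tests, unranked.

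If each is tested at 5% and any one counts as success, the family-wise error is about 15% to 18.5%, and about 9% to 10% for two outcomes at one time point. This rests on that success rule and on correlations of 0 to 0.7 between time points and 0 to 0.5 between outcomes.

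A shortfall in power is not shown. Whether 0.8 is met depends on the alpha finally used, the loss of outcome data and the baseline correlation. The article fixes none of these for the primary analysis.

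**What to change.** Before outcome data are seen:

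1. Name one primary time point, for example T4, with T5 secondary.
2. Test the two primary outcomes at that time point with Holm at a family-wise two-sided 0.05.
3. Restate the power for the alpha actually used, the number expected to be analysed and the planned baseline adjustment, giving the loss rate and the baseline correlation as stated assumptions. The table above shows the range.
4. In the same paragraph, describe the design as 70 clusters with an average size of two.

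The cost is wording, a less favourable stated power in most scenarios (0.72 at the first Holm step with no loss and no adjustment) and the loss of primary status for T5. No extra enrolment is asked for.
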